### Intervention

The intervention package was given for six weeks. The package combined trainer-supervised relaxation exercises (twice per week for 30 minutes/session) and psycho-educational group discussions (twice per week for 75 minutes/session). The order of each session was determined by practical circumstances. The trainer-supervised relaxation exercises consisted of progressive muscle relaxation, guided imagery, stretching and breathing, and progressive resistance exercise. The psycho-educational sessions were divided into directed and semi-structured social support discussion sessions, incorporating problem solving skills building as well as venting. The relaxation exercises were given, over six weeks by trained physical fitness instructors, and the group discussions were given by clinical psychologists and assisted by co-moderates who were social workers. The fitness instructors were trained prior to the intervention by a specialist in muscle relaxation and guide imagery. Similarly, the clinical psychologists received two days of training from a senior clinical psychologist, and were provided with a manual that describes in detail each of the 12 sessions. To ensure coherence among group members, once a group was formed its members remained in the same group throughout the intervention period. The benefits to women enrolled in the trial included: the provision of free childcare during sessions, free pelvic exam, and free laboratory tests.

No major risks were anticipated for the participating women in this trial. There were potentially some discomforting issues, such as repeated pelvic exam and laboratory tests at baseline and at six months, an active commitment to attend sessions throughout the 6 weeks intervention periods, as well as answering some sensitive questions during the interview questionnaires. On the other hand, the control group were provided with a periodic mental health assessment during intervention delivery, free pelvic exam and laboratory tests at baseline and six months.

In particular, for the control (treat later) group, two clinical psychologists monitored them closely (every three weeks) by assessing their depression/suicidal status via administering the Arabic validated Hopkins Checklist-25 (depression subscale, which is comprised of 15 questions to measure depression coupled with an additional question on any plans to commit suicide during the past week). This was perceived to be more ethical to ensure that their CMD status did not worsen during the intervention period for the experimental group. All women with severe depression or who reported plans to commit suicide (whether in the intervention or control group) were referred for free follow-up visits at a community psychiatric clinic, belonging to Medicins Sans Frontier and located in close proximity to Hey el Selloum, in a neighbourhood called Burj el Barajneh.

As for the intervention package, it should be noted that the components and the duration of the intervention package were supported by evidence-based literature findings pertaining to the positive impact of structured social support on disease [48-57] and mental health outcomes [30,38-43,55-57]. The literature also indicates the positive impacts of progressive muscle relaxation and/or guided imagery on mental health and persistent unexplained physical symptoms [44-47].

It should be noted that the particular use of this psychosocial intervention, as opposed to other more sophisticated psychological based methods (cognitive behavioural therapy [CBT] or interpersonal therapy [IPT]), was motivated by the fact that it requires less training and is perceived to be more culturally acceptable, in a conservative-economically disadvantaged Muslim community. The other methods require a larger number of well-trained experts as well as longer training periods before actual implementation, which is beyond the capacities of the trial community. The overarching aim of this trial was to adopt a simple low cost community-based approach (that requires moderate levels of education and experience), with the hope to be later taken over (if proved effective) by the local community centres. It should be noted that the different intervention components were pilot-tested for adequacy, appropriateness and cultural acceptability before actual implementation.

The semi-structured support (SSS) sessions were designed to be partially directed, with semi-structured components. They also incorporated trainings on problem solving and social support. The aim behind this combination was to enable women to participate in the discussion as well as to build rapport. The main desired outcomes of the SSS components were: empathy, venting and problem solving.

The relaxation exercise component of the intervention aimed to train the women on how to engage in guided imagery exercises in their own homes. It was unlikely considered that if the women replicate some of the physical fitness components at home or inform other women about these components (for example some women in the control group) this would result in contamination. Besides, the relaxation exercise sessions were progressive in nature, i.e. did not follow the same routine, starting at 15 minutes and building up resistance to reach 30 minutes. This also contributes to a lower probability of contamination.

Each new session of the relaxation exercise package was designed to wrap up the techniques conducted in the previous sessions, touch upon what is being practiced at home and proceed by adding an additional new technique.

Attendance was continuously monitored at the beginning of each session (SSS and relaxation exercise). A checklist was also used to indicate the techniques learnt in sessions, techniques practised at home, etc.

### Instruments

The primary outcome is MUVD at six months. A woman is considered to have MUVD, if she reports a complaint of vaginal discharge as assessed by the question:" are you complaining currently from vaginal discharge?" and is concurrently not suffering from any RTIs, as confirmed by pelvic exam and laboratory tests (using swabs). Further questions were also asked of the women to note whether or not they are bothered by MUVD, as well as to indicate the colour, odour, thickness, consistency and frequency of discharge. Besides, relevant health service use such as consultations for vaginal discharge and associated treatments were also explored.

#### The secondary outcomes include

- CMD: the Hopkins Symptom Checklist 25 (HSCL-25) (individual scores on anxiety and/or depression > 1.99 are considered symptomatic was used to assess common mental disorders). The HSCL-25 is known to have good psychometric measures [58-61]. This study instrument was field tested for validity and internal consistency on a convenience sample of 153 currently married women, aged 18-49, living in similar conditions in a different area (Ma3amourrah) of the study target group using the MINI International Neuropsychiatric Interview to serve as the diagnostic criteria. For HSCL-25 depression, we recommend the use of 2.10 as the cut off value. This cut off value showed a good balance between sensitivity and specificity, NPV and PPV. It also had the highest kappa value (0.47) among all the other cut offs. As for the HSCL-25 anxiety subscale, the cut off value of choice was 2.00. This value showed a good balance among the various measures and the highest kappa value. The Mini International Neuropsychiatric Interview (MINI) was chosen as the gold standard since it has been validated in Arabic against the Composite International Diagnostic Interview (CIDI) [62]. It has also been validated in Moroccan colloquial Arabic using expert diagnosis by Kadri et al in 2005 [63]. Both validation processes showed that MINI demonstrated good psychometric properties.

- Somatisation: assessed using The Scale for Assessment of Somatic Symptoms (SASS) - the Patel Somatisation Scale, 2005. This scale has been shown to have good psychometric measures in Asian countries [17]. It measures four clusters of somatic symptoms: pain related symptoms (5 questions), sensory somatic symptoms (5 questions), non specific somatic symptoms (5 questions), biological function related symptoms (5 questions). For the purpose of our trial, it was validated by face validity using the expertise of mental health experts.

#### Other measures/cofactors included

- Socio-demographic factors: age, education, employment status, family composition (presence of extended family members), number of children present (by age of each child), housing tenure (owned or rental), number of rooms, and household income.

- Women's reproductive and obstetric history (e.g. pregnancies, live births, abortions, still births).

- Social Support: assessed using questions from the Urban Health Survey, already translated into Arabic.

#### Timing of assessments

Data were collected at the screening phase, at 1.5 months and at six months, with MUVD assessed at baseline and six months. CMDs were assessed at screening, at 1.5 and at six months after randomisation, and somatisation was assessed at baseline and at six months. The laboratory tests to rule out RTIs were assessed at baseline and at six months. The socio-demographic characteristics and reproductive history of the women were assessed only at baseline, while, social support factors were assessed at both baseline and at six months.

### Analyses

The trial will be analyzed and reported in accordance with the CONSORT guidelines. An interim analysis was not planned for this trial. Descriptive statistics will be used to compare the two groups as randomized. The primary analysis will comprise the difference in the percentages of women with MUVD at 6 months between the groups as randomized (including the 95% confidence interval) and the number-needed-to-treat. Logistic regression analyses (for the primary and secondary outcomes) will be used to adjust for any baseline imbalances, and imputation methods will be used to replace missing outcome data. Clustering effects of the intervention groups will be accounted for using methods such as robust standard errors and mixed effects regression models. Potential mediators will be investigated by adding (separately) changes in HSCL-25 Anxiety and Depression sub-scales and the somatisation scale scores to the regression models with the primary outcome. Adherence to the intervention will be accounted for using instrumental variables regression models. Appropriate interaction terms will be added to the regression models for the primary and secondary outcomes to investigate differential effects of the intervention according to age and baseline HSCL-25 scores, all as continuous variables.

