From a woman's perspective, the subjective burden of self-perceived illness and abnormality can be as important as a result of disease due to a biomedical confirmed condition. For example, in Muslim communities, vaginal discharge is considered troublesome because it affects the woman's prayer requirements to be "clean" [7]. Self-perceived illness and abnormality also affect health-seeking behaviour, leading often to unnecessary spending on health care and ineffective management [8,9]. In fact, the syndromic management of vaginal discharge can lead to inappropriate treatment of a large proportion of women, as well as unnecessary spending on treatment of non-existing RTIs [8,13].

An alternative explanation to MUVD has been recently suggested. Several observational studies confirmed the contribution of anxiety and depression to medically unexplained gynaecological symptoms, such as pelvic pain and abnormal vaginal discharge [5,12,14-22]. Taking the already discussed UHS, the sub-sample analysis pertaining to Hey el Selloum sample, showed that a large proportion of women (42%) reported mental distress- as assessed by GHQ-12. Moreover, multivariate analysis showed that mental distress was significantly associated with reported abnormal vaginal discharge, after adjusting for relevant risk factors and reported RTIs [23]. Women considered stress to be a main cause of their discharge [24] and identified mental as well as psychological health as important elements contributing to their perception of good reproductive health [4]. The UHS also showed that both mental distress and reported gynaecological health problems were negatively associated with social support [25].

Along the same line, population-based studies from South Asia show significant associations between complaints of vaginal discharge and psychosocial stress, in addition to psychosomatic symptoms such as dizziness, backache, and weakness [12,14,26]. Qualitative studies in India indicated that women typically associate complaints of discharge with mental stress and related symptoms such as tiredness [12]. On the other hand, social support is consistently associated with common mental disorders (CMD) and physical conditions [27]. Improvements in social support were shown to lead to lower consultation rates [27,28] and reduced sickness absences [29].

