### Sample Size

The sample size calculation was based on the primary outcome of reported MUVD at six months. Allowing for 10% attrition, a sample size of 80-102 in each group would provide 80-90% power to detect a difference of 20 percentage points (for example, 10% vs. 30%) in the proportion reporting MUVD at 6 months, using a 2-sided 5% significance level. There is no previous study that can directly inform the effect size likely for this outcome, but studies have found differences in recovery rates for CMD of up to 40% between usual care and active interventions for common mental disorders (4, 10, 11). We have opted for a 20 percentage point difference given these previous studies on CMD and our judgement that this is both a clinically significant and plausible difference in MUVD rates.

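### Covariates for the supportive adjusted models are chosen by observed baseline imbalance, which makes those estimates data-dependent and forgoes precision from baseline scores already collected

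*Protocol article*

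**What the plan says.** The Analyses section of the protocol article fixes an unadjusted primary analysis: "The primary analysis will comprise the difference in the percentages of women with MUVD at 6 months between the groups as randomized", with a 95% confidence interval and the number needed to treat. It then adds supportive models: "Logistic regression analyses (for the primary and secondary outcomes) will be used to adjust for any baseline imbalances". It names no adjustment covariate, no definition of imbalance and no limit on the number of covariates. The comparison of the arms at baseline is to be descriptive.

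Candidate covariates are already collected. Under Timing of assessments: "CMDs were assessed at screening, at 1.5 and at six months after randomisation, and somatisation was assessed at baseline and at six months". Age and other socio-demographic factors, reproductive history and social support are also recorded at baseline. In the Analyses section, age and baseline HSCL-25 are named only for interaction terms, and changes in HSCL-25 and somatisation only for mediation.

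The Background gives a reason to expect mental distress to matter: "multivariate analysis showed that mental distress was significantly associated with reported abnormal vaginal discharge".

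**The concern.** Whether a covariate is worth adjusting for depends mainly on how strongly it predicts the outcome. In a randomised comparison, observed imbalance is a poor guide to that. A strong predictor that happens to be balanced still reduces the variance of the treatment effect, while an imbalanced variable unrelated to the outcome adds nothing. A rule based on imbalance therefore tends to omit useful variables and admit useless ones, and the model cannot be written down until the baseline table has been seen.

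At stake are the adjusted estimates for the primary and secondary outcomes: whether they were fixed in advance, and how precise they are. The primary risk difference is not at stake.

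**Working it through.** **1. Inputs.** The Sample Size section states: "Allowing for 10% attrition, a sample size of 80-102 in each group would provide 80-90% power". The same section gives example rates of 10% and 30%, tested two-sided at 5%. Equal allocation is inferred, because one size range is given for both arms.

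**2. The plan's own figure.** For two proportions, n = [z(α/2)·√(2p̄q̄) + z(β)·√(p1q1 + p2q2)]² / d², with p1 = 0.10, p2 = 0.30, p̄ = 0.20 and d = 0.20.
- 80% power: (1.960·√0.32 + 0.842·√0.30)² / 0.04 gives 62 per arm, or 72 with continuity correction.
- 90% power: 82 per arm, or 92 with continuity correction.
- Attrition: 72/0.9 = 80; 92/0.9 = 102.2, rounded up to 103 (92 × 1.1 = 101.2 gives 102).

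The stated 80-102 per arm is reproduced with the continuity correction. It rests on an unadjusted comparison and does not depend on the covariate rule.

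**3. Events available.** At 10% vs 30%: 72 × (0.10 + 0.30) = 28.8, about 29 events; 92 × 0.40 = 36.8, about 37. A model with treatment, age and one HSCL-25 score has 29/3 = 9.7 to 37/3 = 12.3 events per term. With both subscales it has 29/4 = 7.2 to 37/4 = 9.2.

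**4. Simulation of the rule.** Assumptions not in the protocol: 72 women analysed per arm; ten independent standardised baseline covariates, one of them prognostic; imbalance defined as t-test p < 0.05; no clustering; log-odds ratio per SD of the prognostic covariate 0, 0.5, 1.0 or 1.5 (odds ratios 1, 1.6, 2.7, 4.5). There were 2,500 runs per setting.

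Power at 30% vs 10%:

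| Log-OR per SD | Unadjusted | Chosen by imbalance | Score fixed in advance |
|---|---|---|---|
| 0 | 87.1% | 86.1% | 86.6% |
| 0.5 | 87.6% | 87.1% | 88.7% |
| 1.0 | 85.5% | 85.8% | 90.4% |
| 1.5 | 87.3% | 87.2% | 92.9% |

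Standard deviation of the risk difference (standardised for the adjusted models):

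| Log-OR per SD | Unadjusted | Chosen by imbalance | Fixed in advance | Variance change, fixed vs unadjusted |
|---|---|---|---|---|
| 0 | 0.0641 | 0.0648 | 0.0644 | about +1% |
| 0.5 | 0.0636 | 0.0639 | 0.0630 | about −2% |
| 1.0 | 0.0651 | 0.0643 | 0.0613 | about −12% |
| 1.5 | 0.0648 | 0.0639 | 0.0584 | about −19% |

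The last column is (SD fixed / SD unadjusted)² − 1; for example, (0.0584/0.0648)² = 0.81.

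The imbalance rule performs much like no adjustment. A 5% test admits the prognostic score in only about 5% of randomisations, by construction.

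**5. Type I error (30% vs 30%).** The imbalance-chosen analysis rejected in 4.2% to 5.0% of runs (Monte Carlo error about 0.4 points), so there is no inflation. Reporting whichever of the three analyses was most favourable would reject in 5.6% to 7.4%.

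**6. Secondary scores.** For HSCL-25 and somatisation, each outcome's own baseline value is available. For MUVD it is not usable, because eligibility requires MUVD in every woman at entry. No gain is computed for the secondary scores, because the protocol gives no baseline-to-follow-up correlation.

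**The case against.** The strongest reply is that these models are supportive, the primary result is fixed and unadjusted, and a covariate list is commonly left to an analysis plan. The first two points stand and limit the matter. The third does not remove it: the protocol states a selection principle, and that principle is poor. The protocol does not expressly bar other covariates, but imbalance is the only criterion it gives.

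A second reply is that the precision loss is assumed. This also stands. The association in the Background comes from a survey that used GHQ-12 among ever-married women, not from persistence of MUVD over six months. Excluding women with very low or severe scores narrows the HSCL-25 range and may weaken prediction further. The larger gains in the tables need odds ratios of about 2.7 to 4.5 per SD.

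A third reply is specific to this trial. Women learned their allocation before giving written consent, so imbalance may reflect selection and not only chance. That is a sound reason to examine imbalance in a sensitivity analysis. It is not a reason to let imbalance define the main adjusted model.

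A reader might go further than the document allows in three ways:
- **False imbalances.** Counting 16 baseline variables gives 1 − 0.95^16 = 56% for at least one chance imbalance. The plan states no 5% test, several of the variables are plainly related, and the reproductive items are only examples.
- **Effective sample size.** Dividing 80 by 0.90 or 0.80 gives an effective 89 to 100 women per arm. This applies a linear-model formula to a binary outcome, starts from women enrolled instead of the 72 analysed (which would give 80 to 90), and assumes the prognostic strength.
- **Scale.** The protocol does not say that the adjusted effect will be reported as an odds ratio. A logistic model can also yield a risk difference.

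**Conclusion.** The point holds as an inexpensive improvement to the supportive analyses. The imbalance rule makes the adjusted estimates data-dependent and recovers almost none of the precision available from prognostic baseline scores.

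For MUVD, fixing a prognostic score in advance would reduce variance by about 2% to 19% and add about 1 to 6 points of power, if its log-odds ratio per SD lies between 0.5 and 1.5. There is no gain if it is not prognostic. These figures rest on independent covariates, a 5% imbalance test, 72 women per arm and no clustering, none of which the protocol states for this purpose except that 72 follows from its sample size. The gain is more plausible for the HSCL-25 and somatisation outcomes, but cannot be sized.

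A reader might infer that the primary result is compromised or that false-positive risk rises. The documents do not support either. The primary risk difference is unadjusted, and the rule kept type I error at 4.2% to 5.0%. The higher 5.6% to 7.4% needs a free choice among analyses, which naming the primary analysis rules out.

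**What to change.** In the Analyses section, replace the imbalance criterion with a short covariate set used in every adjusted model whatever the observed balance:
- **All outcomes:** age and baseline HSCL-25, both continuous. Use a single total HSCL-25 score if events are too few for both subscales, as the 29 to 37 expected MUVD events suggest.
- **HSCL-25 and somatisation outcomes:** add that outcome's own baseline value where it is not already included.
- **MUVD:** report the adjusted effect as a risk difference by marginal standardisation from the logistic model, beside the unadjusted primary result, with the allowance for intervention-group clustering that the section already promises.
- **Other observed imbalances:** adjust for them only in a labelled sensitivity analysis, citing the disclosure of allocation before written consent as its rationale.

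The cost is one paragraph, settled before outcome data are examined by arm. It needs no new data and does not change the sample size or the primary analysis.

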#### Study Inclusion Criteria

- Currently married women, 18-49 years of age

- Women who reported symptoms of vaginal discharge confirmed by medical exam to be MUVD

- Women who scored low to moderate levels of Common Mental Disorders (CMDs), based on the study screening tool for common mental disorders (Hopkins Checklist 25)

- Women who were willing to take part in the study by signing an informed consent after listening to our explanation of the study process

- Women who upon screening had none of the exclusion criteria listed below

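### Logistic regression is the only model named for secondary outcomes that are scores: somatisation has no defined event, the HSCL-25 depression cut-offs conflict, and precision is lost

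*Protocol article*

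**What the plan says.** All references are to the protocol article.

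- **Analyses.** The regression sentence opens "Logistic regression analyses (for the primary and secondary outcomes" and gives adjustment for baseline imbalance as the purpose. The next regression methods named are robust standard errors and mixed effects models, introduced for clustering by intervention group, with no link function given. No linear treatment comparison of a secondary score is stated.
- **The secondary outcomes include (HSCL-25).** The outcome definition is "individual scores on anxiety and/or depression > 1.99 are considered symptomatic". Reporting the field test, the same bullet says for depression that "we recommend the use of 2.10 as the cut off value" and for anxiety that "the cut off value of choice was 2.00". Of the 2.10 depression cut-off it says "It also had the highest kappa value (0.47) among all the other cut offs".
- **The secondary outcomes include (somatisation).** Of the scale it says "It measures four clusters of somatic symptoms", with five questions in each cluster, so 20 items. No threshold appears.
- **Analyses, later sentences.** Changes in the HSCL-25 subscales and in the somatisation score enter the primary-outcome models as mediators. Baseline HSCL-25 enters the interaction models as a continuous variable.
- **Timing of assessments.** HSCL-25 is measured at screening, 1.5 and six months; somatisation at baseline and six months.

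**The concern.** Logistic regression needs a yes/no outcome. Somatisation has none, so the model cannot be run as written until someone chooses a threshold, possibly with the data in view. The HSCL-25 has a yes/no rule, but for depression the document gives two different ones.

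Reducing a score to above or below a cut-off also discards information. The trial's rationale is that the intervention reduces discharge complaints by reducing distress, so the effect of treatment on distress is the first link in its argument. A less efficient test makes it more likely that a real effect on distress is reported as inconclusive. The plan already treats the same scales as continuous when they serve as mediators or modifiers, so the treatment comparison is on a different and weaker scale than the rest of the analysis.

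**Working it through.** **1. The plan's own figure.** Sample Size gives 80–102 per group for 10% vs 30%, two-sided 5%, 80–90% power and 10% attrition. The two-proportion formula gives 61.6 (80% power) and 82.0 (90%) per arm; with continuity correction, 71.2 and 91.7. Dividing by 0.9 gives 79.2 and 101.9, i.e. 80 and 102. The figure is reproduced. The evaluable numbers are therefore 72 and 92 per arm. The article gives no power figure for the secondary outcomes.

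**2. The cut-offs side by side.** The section on the intervention gives the depression subscale 15 questions. If items are scored in whole numbers and averaged (assumption), the subscale moves in steps of 1/15. Totals of 30 and 31 give means of 2.00 and 2.07: symptomatic under > 1.99, not symptomatic under 2.10. For anxiety, with the remaining 10 items, scores move in steps of 0.1, so > 1.99 and a cut-off of 2.00 read as at or above coincide. The conflict is therefore in depression.

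**3. Information kept after dichotomising.** For a normal score (assumption) with share p above the cut-off (not in the documents), relative efficiency is E = φ(z_p)² / [p(1 − p)].

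| p | φ(z_p) | E | Loss |
|---|---|---|---|
| 0.5 | 0.399 | 0.1592/0.25 = 0.637 | 36% |
| 0.3 | 0.348 | 0.1209/0.21 = 0.576 | 42% |
| 0.2 | 0.280 | 0.0784/0.16 = 0.490 | 51% |

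The smallest loss under normality is at p = 0.5.

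**4. Power for an assumed 0.4 SD effect, two-sided 5%, clustering ignored.**

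*Continuous:* power = Φ(0.4/√(2/n) − 1.96).
- n = 72: Φ(2.40 − 1.96) = 67%.
- n = 92: Φ(2.71 − 1.96) = 77%.

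*Continuous, adjusted for baseline with correlation 0.5 (assumption):* the SD shrinks to √(1 − 0.25) = 0.866.
- n = 72: Φ(2.77 − 1.96) = 79%.
- n = 92: Φ(3.13 − 1.96) = 88%.

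*Binary:* the control share p_c above the cut-off is assumed, and p_t follows from a 0.4 SD shift. Power = Φ{[p_c − p_t − 1.96√(2p̄(1 − p̄)/n)] / √([p_c(1 − p_c) + p_t(1 − p_t)]/n)}.

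| p_c | p_t | n = 72 | n = 92 |
|---|---|---|---|
| 0.5 | 0.345 | 47% | 57% |
| 0.7 | 0.550 | 46% | 56% |
| 0.3 | 0.178 | 40% | about 50% |

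At n = 72, other assumed effects give the same ordering. At 0.3 SD power is about 26–30% binary against 44% continuous. At 0.5 SD it is about 56–65% against 85%.

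**5. Like for like, with baseline adjustment on both sides.** A simulation (82 per arm, 0.4 SD, correlation 0.5, 1,500 runs per setting) compared logistic regression adjusted for the baseline score with linear ANCOVA. Power was 61% vs 86% at p_c = 0.5, 51% vs 84% at 0.3 and 39% vs 84% at 0.2. The corresponding information losses were about 47%, 58% and 68%. Adjusting the logistic model for baseline does not close the gap.

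**The case against.** The best defence is that caseness on a field-tested scale is a legitimate and readable secondary outcome, and it may have been deliberate: Sample Size discusses earlier work in terms of recovery rates for common mental disorders. The regression sentence concerns adjustment for baseline imbalance, the mixed models named next could be linear, and a condensed article may leave scoring to a full protocol or analysis plan not shown.

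Much of this stands. The binary HSCL-25 analysis is inefficient, not invalid, and an unseen document could supply a somatisation threshold. But the article does not leave the model open: it names logistic regression for the secondary outcomes. It also prints two depression cut-offs in one bullet.

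Four stronger readings are tempting and are not supported:

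- **That at least 40% of the information is lost.** Under normality the minimum is 36%. The actual loss depends on the share above the cut-off and the shape of the scores, neither of which is given.
- **That women entering below the cut-off make improvement undetectable.** Entry is described as "Women who scored low to moderate levels of Common Mental Disorders (CMDs", very low scorers are excluded, and no numeric bounds are given. How many women, if any, entered below 1.99 is unknown.
- **That mediation cannot be interpreted.** The mediators enter as score changes, not as caseness.
- **That the somatisation score is dichotomised.** No text says so; the named model simply has no event to act on.

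The kappa of 0.47 also belongs to the 2.10 depression cut-off, so it cannot be quoted as the agreement of the > 1.99 rule.

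**Conclusion.** The point holds as a matter of efficiency and definition in the secondary analysis. Two parts need no assumption: the only model named has no defined event for somatisation, and the HSCL-25 depression cut-offs disagree. The third part, lost precision, is at least about 36% of the information if scores are roughly normal, or around 20 to 27 percentage points of power for a 0.4 SD effect before any baseline adjustment (67% against 40–47% at 72 per arm; 77% against 50–57% at 92). Normality, the share above the cut-off, the effect size and the baseline correlation are all assumptions, and the power figures ignore clustering. The primary outcome and its sample size are not affected. The change is worth making because it is nearly free and removes dependence on a disputed cut-off.

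**What to change.** Before the arms are compared on these outcomes, amend the Analyses text as follows:

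1. Analyse HSCL-25 depression and anxiety scores at 1.5 and six months, each in a baseline-adjusted repeated-measures mixed model (or ANCOVA at each time), and the somatisation total at six months in a baseline-adjusted linear model.
2. Apply the same allowance for clustering by intervention group as for the primary outcome.
3. Keep logistic regression for the primary outcome. Report the percentage above the HSCL-25 cut-off as a supplement, after reconciling the > 1.99, 2.10 and 2.00 statements and fixing one rule per subscale.

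The cost is wording and some programming; the scores are already collected. The one downside is that a mean difference is less directly readable than caseness, which the supplement covers. If scores prove clearly skewed, robust standard errors, already among the methods named, can be used for the linear models.
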